#### Intervention Fidelity, Controlling for Bias, and Optimizing Internal Validity

We aim to optimize internal validity by asking providers about their involvement in other care transition interventions during the evaluation and in the 12 months prior to the study. We will also track readmitted patients who already used the Digital Bridge, as patients with CCN can have frequent hospital visits, without altering data collection time frame from index admission.

Our previous work identifies a need to balance real-world implementation and maintaining methodological rigor [78,79]. To accomplish this, we will distinguish core components of the intervention (what is determined to be central to success) from adaptable components [79]. This is an established approach to intervention fidelity in highly complex interventions such as this one [80,81]. Complex interventions often need to be continually adapted to local contexts and changing environments [82]. Attending to our third research question will support this work.

#### Implementation Measures

Implementation relates to the processes required to put an intervention or new model of care into use [79]. An implementation lens identifies context and process variables likely to influence intervention outcomes, known to be important in studies of digital health interventions [83]. Context and process data will additionally support the development of a scale and spread strategy [84] and is consistent with a developmental evaluation approach [59]. We will adopt the Consolidated Framework for Implementation Research (CFIR) [79], which compiles constructs that have been associated with effective implementation of complex interventions (see Figure 3 [79]).

An embedded ethnographic comparative case study methodology will be adopted, aligned with the case study approach of Yin [85] and the ethnographic approach to evaluating technology of Greehalgh [86]. Each site/service combination is considered a single case (8 cases total). Interviews with patients and caregivers (subset of 5 patients and caregivers from each unit, 40 patients and 40 caregivers total) and focus groups with providers and managers (6 to 8 participants per group [87]) will be conducted, along with a review of relevant organizational documents (eg, annual reports and vision statements) and observations of provider interactions and patient-provider interactions (eg, rounds, care planning meetings, clinic visits).

**Figure 3 figure3:**
[figure not shown]
Consolidated framework for implementation research constructs (adapted from Damschroder [79]).

### Data Analysis Strategy

#### Phase 1: Workflow Analysis

Consistent with established user-centered co-design methods, we will adopt an interpretive descriptive approach to analyze focus group data and iteratively design the workflow [88]. Analysis will guide modifications and integration of the Care Connector and ePRO technologies into the Digital Bridge. Feasibility and usability will be assessed using standard descriptive statistics across 3 domains of the PSSUQ. Demographic information collected from participants will inform analysis and support transferability to other settings.

#### Phase 2: Developmental Evaluation and Implementation Analysis

We will adopt a multimethod case study analysis approach [85], looking at within and between group assessments (Figure 4), accounting for hospital/service specific context variables. Single case and cross-case comparative analyses will be used to assess context, process, and outcome measures.

**Figure 4 figure4:**
[figure not shown]
Within and between group pre-post analysis.

For quantitative outcome measures (eg, CTM-3, relational coordination, AQoL-4D), statistical comparisons between the pre- (baseline) and post- (intervention) data will be made using mixed-effects regression models to account for potential clustering effect of patients from the same service. As this is a complex intervention and local context/implementation factors may affect outcomes, we will perform sensitivity analysis and examine each of the participating services separately. For repeated measures within the same individual, we will use a difference in differences approach (eg, AQoL-4D measured at 0, 2 weeks, 1 month, and 6 months post-discharge). Patients may experience decline in QoL over time in both control and intervention groups for reasons unrelated to the intervention; a lesser magnitude of decline in intervention versus control group may suggest a benefit of the intervention.

For patients who do not complete a study follow-up, we will analyze all available data points. Additionally, understanding the characteristics (via collected demographic and administrative data of this study) of those who do not complete follow-up may inform us of under what conditions and for whom the technology works best.

Qualitative data will be analyzed using an ethnographic case study approach [86], adopting techniques such as interpretive descriptive coding methods and word tables [85] to support the within and cross case analysis as used in previous evaluations and similar case comparisons [33,48]. Two researchers trained in qualitative research will read interview and focus group transcripts and field notes, record key themes, compare, and discuss findings. Both inductive and deductive analysis techniques will be used to identify themes and then conceptually map with the CFIR theoretical framework. NVivo software (QSR International) will be used for qualitative data management.

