**Methods:**

The study includes two phases: workflow co-design (phase 1), followed by implementation and evaluation (phase 2). Phase 1 will include iterative co-design working groups with patients, caregivers, hospital providers, and primary care providers to develop a transition workflow that will leverage the use of Care Connector and ePRO to support communication through the transition process. Phase 2 will include implementation and evaluation of the Digital Bridge within two hospital systems in Ontario in acute and rehab settings (600 patients: 300 baseline and 300 implementation). The primary outcome measure for this study is the Care Transitions Measure–3 to assess transition quality. An embedded ethnography will be included to capture context and process data to inform the implementation assessment and development of a scale and spread strategy. An Integrated Knowledge Translation approach is taken to inform the study. An advisory group will be established to provide insight and feedback regarding the project design and implementation, leading the development of the project knowledge translation strategy and associated outputs.

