### Study Design

We will conduct a nonrandomized controlled trial to understand the impact of the intervention. For each site (SHS and THP) and each service (acute medicine and rehab), half of the participating wards will be designated as control while the other half will be designated as intervention (4 wards per hospital for a total of 8 wards). Quasi-experimental (or nonrandomized) design is often used in medical informatics evaluation due to insufficient sample size for cluster-randomized design [60] and complexity of intervention [61]. We have chosen to designate intervention wards together with operational leaders at each organization rather than randomize wards to increase the chance of successful implementation. While this could introduce selection bias into the study, it is felt this risk is worthwhile given that one important barrier to adoption of information communication technologies in hospitals is lack of readiness for implementation [62-64]. If clinical units that are not ready to take on a new technology implementation are randomized into the intervention group, we may experience a feasibility barrier that could derail the study before it begins. Our mixed-methods approach has been designed to capture important characteristics of the included clinical wards so that any potential selection bias can be understood.

General medicine units at both organizations serve a complex and clinically diverse population, with a median age of 73 (IQR 57-84) years and a median of 6 (IQR 3-9) coexisting medical conditions [65]. They care for patients with a wide variety of diagnoses (more than 200 distinct diagnoses) with the top 10 diagnoses comprising 36.2% of hospitalizations [66]. Rehabilitation services across the two organizations admit patients due to stroke, musculoskeletal concerns, and complex medical needs. At THP, services are not diagnosis-based; at SHS, however, patients are clustered on wards with specialized services.

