We will collect baseline data from all wards (control and intervention) during phase 1 while co-design is ongoing and the intervention has not been deployed. During phase 2, after co-design is complete, the co-designed technology intervention and workflow will be rolled out to only the intervention wards. We will then collect data (identical to what was collected at baseline) from all wards (control and intervention) to understand the impact of technology by examining the differential change in control and intervention wards between baseline and intervention periods (difference in differences approach).

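### The protocol names no patient-level confounder adjustment for the primary nonrandomized CTM-3 comparison, so a case-mix change that differs between ward groups would enter the estimate

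*Protocol article*

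**What the plan says.** All references are to the Protocol article.

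- **Allocation (Study Design).** "We have chosen to designate intervention wards together with operational leaders at each organization rather than randomize wards". The section accepts that this may introduce selection bias. Its response is that the mixed methods will "capture important characteristics of the included clinical wards so that any potential selection bias can be understood".
- **Contrast (Study Design).** The effect is the difference in differences: change from baseline to intervention period on intervention wards, against the same change on control wards.
- **Samples (Abstract, Methods; Population and Recruitment).** The plan is for "600 patients: 300 baseline and 300 implementation", recruited at admission.
- **Outcome timing (Table 1).** CTM-3 is taken 1 to 2 weeks after discharge, once per patient.
- **Model (Data Analysis Strategy, Phase 2, quantitative paragraph below Figure 4).** CTM-3 and the other quantitative outcomes are analysed with "mixed-effects regression models to account for potential clustering effect of patients from the same service". Each service is also examined separately as a sensitivity analysis. The case-study analysis is described as "accounting for hospital/service specific context variables".
- **Bias control (Intervention Fidelity, Controlling for Bias, and Optimizing Internal Validity).** The measure given here is: "We aim to optimize internal validity by asking providers about their involvement in other care transition interventions". Readmitted patients who have already used the Digital Bridge are also tracked.
- **Patient data at hand (Table 1, patients and caregivers).** A patient information sheet at recruitment records demographics, complexity, social support and ease with technology. It is listed under the implementation question. In the Phase 2 quantitative text, demographic and administrative data are used to describe patients who do not complete follow-up.

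**The concern.** Because no patient has a CTM-3 value from before the intervention, the design cannot compare patients with themselves. The baseline and intervention periods are two separate samples from each ward. If the patients enrolled on intervention wards in phase 2 differ from those enrolled at baseline in a way not matched on the control wards, and the difference matters for how a transition is rated, the estimate absorbs it.

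The document gives reasons to take this seriously. Wards were chosen with operational leaders partly for readiness. Within one service the wards may serve different populations: for rehabilitation, "at SHS, however, patients are clustered on wards with specialized services". Patients with mild cognitive impairment may join if they can consent and can use the intervention, alone or with a caregiver; only the intervention wards in phase 2 have an intervention to use. The text does not say how recruiters would apply that criterion in the other groups, so selection of better-supported patients into that one group is a possibility, not a stated fact. The Discussion also expects system and organizational change during the study.

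At stake is whether a gain in CTM-3 can be attributed to the Digital Bridge or partly to who was enrolled.

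**Working it through.** **1. Is there a figure to reproduce?** The plan gives none for confounding. Its sample size neither tests nor depends on this point. Only these inputs are taken from it: an anticipated effect of 13 points (lower end of 13 to 14) and an SD of 21.4 (Sample Size Calculation); 300 patients per period (Abstract); and half of the wards in each group (Study Design). Assuming equal recruitment, that is 300 / 2 = 150 patients per ward-group-by-period cell.

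**2. What the contrast removes.** Write the mean CTM-3 in ward group g and period t as

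ward effect(g) + period effect(t) + δ (intervention wards, phase 2 only) + γ × m(g,t),

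where m is the proportion of patients with some characteristic and γ is the CTM-3 gap between patients with and without it. The difference in differences is

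δ + γ × {[m(I, post) − m(I, base)] − [m(C, post) − m(C, base)]}.

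Ward and period effects drop out. The term in braces, the differential shift in case mix, does not.

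**3. Does any stated measure remove that term?**
- A random effect for service addresses correlation within a service. It does not remove patient mix that differs between ward groups and periods inside that service.
- Ward characteristics are collected so that bias can be understood. No modelling step is attached.
- Provider reports concern other interventions, and tracking of readmitted users concerns repeat exposure. Neither concerns who is enrolled.
- Hospital and service context variables are above patient level.
- Separate service analyses still compare intervention with control wards within a service, so the term remains in each.
- Common eligibility rules narrow the range of patients but still allow wide variation in support, complexity and ease with technology.

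**4. How large could it be?** Neither the shift nor γ is in the document, so both are assumptions. Bias = shift × γ.
- Low: 0.10 × 5 = 0.5 points; 0.5 / 13 = 4% of the anticipated effect.
- High: 0.30 × 15 = 4.5 points; 4.5 / 13 = 35%.

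For scale, the standard error of the pooled contrast, ignoring clustering, is 21.4 × √(4/150) = 3.49 points. The bias is then 0.5 / 3.49 = 0.14 to 4.5 / 3.49 = 1.29 standard errors. By the normal approximation Φ(−1.96 + b/SE) + Φ(−1.96 − b/SE), a nominal 5% two-sided error becomes about 5.2% at the low end and 25% at the high end.

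**5. Cross-check with a continuous case-mix score.** Bias = √R² × 21.4 × shift in SD units, with R² the share of CTM-3 variance the score explains (assumed).
- R² 2%, shift 0.1 SD: 0.141 × 21.4 × 0.1 = 0.3 points.
- R² 10%, shift 0.3 SD: 0.316 × 21.4 × 0.3 = 2.0 points, error about 8.9%.
- R² 20%, shift 0.5 SD: 0.447 × 21.4 × 0.5 = 4.8 points, error about 28%.

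Both routes give a range from negligible to roughly a third of the target effect.

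**The case against.** The strongest reply is that the quoted sentence is a summary. It explains why a mixed model was chosen and lists no fixed effects at all, not even the ward-group and period terms that Study Design requires. A covariate list is an ordinary item for a statistical analysis plan, which is not shown, and a condensed article need not carry it. Nothing in the text forbids covariates or calls an unadjusted estimate primary.

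That stands as far as it goes. A reader might infer that the protocol has decided to leave patient covariates out of the model; the document does not support this, because it is silent. A reader might also infer that the estimate will be biased by some known amount; that is not supported either, because every bias figure above rests on assumed inputs. Chance imbalance adds nothing to the argument, since ordinary sampling variation is already covered by the standard error.

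The design also has real protection: concurrent control wards, the same eligibility rules throughout, and an open statement of the selection risk.

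The reply does not fully answer the point, however. The article sets out its own approach to selection bias in Study Design and in a section whose title promises bias control. Followed as written, that approach contains no step at patient level.

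**Conclusion.** The point holds in a limited form. For a nonrandomized primary comparison of different patients in each period, the protocol names no patient-level adjustment, although suitable data are recorded at recruitment. A case-mix change that differs between ward groups would pass into the CTM-3 estimate from the model as described. Its size is unknown; 0.5 to 4.5 points against 13 is an illustration under an assumed 10 to 30 percentage-point shift and a 5 to 15 point CTM-3 gap, with an unclustered standard error used for scale.

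Adjustment would reduce only the part of the bias due to measured characteristics. This is an inexpensive improvement that should be made, not a defect that invalidates the design. If an unpublished analysis plan already fixes such a list, a one-line statement in the protocol is enough.

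**What to change.** In the Phase 2 quantitative analysis paragraph:

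- State that the mixed model for CTM-3 contains ward group, period and their interaction, plus a short prespecified set of characteristics recorded at recruitment. Examples are age, sex, number of the listed chronic conditions, social supports and comfort with technology. The exact list is a judgement; what matters is that it and its coding are fixed before phase 2 outcomes are seen.
- Apply the same rule to the other patient-level outcomes compared between ward groups, such as AQoL-4D and days at home.
- Make the adjusted estimate primary and report the unadjusted one as a sensitivity analysis.
- Tabulate the covariates by ward group and period, so that any differential shift is visible.
- Keep the list shorter in the separate service analyses, where groups are small.

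Cost: analysis wording only, with no new patients, visits or instruments if the information sheet is used as described. The downside is a few degrees of freedom and a simple stated rule for missing covariate values.

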### Population and Recruitment

Patients will be recruited at the time of admission to one of the services (acute medicine or rehab) in the study. Patients aged 60 years and over, with CCN defined as presenting with 3 or more chronic conditions from the 16 most prominent in the population: arthritis (except rheumatoid arthritis), chronic coronary syndrome, dementia, hypertension, cardiac arrhythmia, rheumatoid arthritis, asthma, osteoporosis, stroke, depression, chronic obstructive pulmonary disease, acute myocardial infarction, diabetes, congestive heart failure, cancer, and renal failure.

This method is aligned with current and established methods to identify patients with CCN [67-69]. Patients must be slated to be discharged home. As the technology is only currently available in English, patients (or a caregiver) must be able to speak and read English. Patients with mild cognitive impairment will not be excluded if able to provide informed consent and engage with the intervention (independently or with caregiver aid). During phase 1, all recruited patients will receive usual care. During phase 2, recruited patients from the intervention wards will receive the Digital Bridge intervention while those from control wards will receive usual care. Family/caregivers of recruited patients may be invited to participate in qualitative interviews.

As workflow integration is a foundation for implementing technology, all hospital providers on the general medicine and rehabilitation services will be invited to participate. PCPs of recruited patients will be contacted and invited to participate while the patient is still in hospital. Recruited patients may still participate in the study if their PCP does not wish to participate or if they do not have a PCP at the time of study enrollment. Should the PCP choose to join, they will be consented and trained to adopt the technology to support their patients post-discharge if their patients were recruited from the intervention wards during phase 2.

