#### Sample Size Calculation

Patient participants will be grouped into 1 of 4 arms (as determined by the unit they were discharged from) in both the baseline (pre-intervention) and postintervention periods. Our primary outcome, CTM-3, is scored as a continuous variable (0 to 100%) based on a published algorithm [77]. THP pilot data with 107 patients showed a baseline CTM-3 score of 74% (SD 21.4; unpublished). Our sample size calculation is based on an anticipated 13% to 14% increase in CTM-3 score and a standard deviation of 21.4 (derived from our previous studies of Care Connector). To ensure analysis for each of the 8 subgroups to be significant, we required a higher sample size than would be required in typical drug trials where randomization occurs at the individual level. As such we will recruit 33 to 38 patients per group; 8 groups in baseline (264 to 304) and 8 groups in intervention (264 to 304) for a total of 528 to 608 (based on *P*=.05 and power of .80).

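### The CTM-3 model clusters patients by service, but the intervention is assigned by ward, so variation at the level of assignment is not covered and the test is anti-conservative if wards vary between periods

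*Protocol article*

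**What the plan says.** Four statements in the protocol article bear on this point.

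- **Assignment.** Under Study Design, within each site and service, "half of the participating wards will be designated as control while the other half will be designated as intervention", which gives "4 wards per hospital for a total of 8 wards".
- **Meaning of service.** Study Design and Population and Recruitment both use the word for the clinical stream: "Patients will be recruited at the time of admission to one of the services (acute medicine or rehab) in the study".
- **Effect.** The end of Study Design describes the impact as "examining the differential change in control and intervention wards between baseline and intervention periods (difference in differences approach"), so the contrast is between wards and across periods.
- **Model.** For CTM-3, relational coordination and AQoL-4D, Phase 2: Developmental Evaluation and Implementation Analysis names mixed-effects regression "to account for potential clustering effect of patients from the same service". No ward or ward-by-period term is mentioned.

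The Sample Size Calculation acknowledges that more patients are needed than under individual randomization, but it gives no ICC and no design effect.

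**The concern.** The analysis should carry variation at the level where treatment is assigned. Two sites with two services each make 4 site-service combinations. With 4 wards per hospital, and each service split in half, every combination has exactly one control and one intervention ward. An effect for service, whether counted as 2 services or 4 site-services, adds the same amount to both arms and drops out of the treatment contrast.

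Stable differences between wards also drop out, because each ward is compared with its own baseline. What remains is ward-by-period variation: one ward improving or worsening between the periods for reasons unrelated to the intervention. The protocol expects such influences. The Phase 2 analysis section says that local context and implementation may affect outcomes. Strengths and Limitations anticipates practice changes, uneven adherence, clinicians rotating between units, and policy and organizational change. If this variation is present and not modelled, the standard error for the primary outcome is too small, and a chance result could feed the planned scale-and-spread strategy.

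**Working it through.** **Inputs from the protocol.** 8 wards, 4 per arm; 2 periods; n = 33 to 38 patients per group and period; "anticipated 13% to 14% increase in CTM-3 score and a standard deviation of 21.4". The outcome is continuous: "Our primary outcome, CTM-3, is scored as a continuous variable (0 to 100%).

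**The plan's own figures.** The totals reproduce: 16 × 33 = 528 and 16 × 38 = 608. The per-group range does not follow from a single formula. A two-sided comparison of two means at 80% power needs 37 per group for 14 points (38 with the t distribution) but 43 for 13 points (44 with t). That is a separate matter; the stated 33 to 38 is taken as given here.

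**Assumptions.** ρw is the stable ward ICC and ρwp the ward-by-period ICC. The document gives neither, so a range is shown. The test is taken as a two-sided large-sample test from a model with a service effect and no ward-by-period term.

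**Formulas.**

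1. Variance of one arm-period mean, leaving out the stable ward part that cancels: SD² × [ρwp/4 + (1 − ρw − ρwp)/(4n)].
2. The difference in differences combines four such means: true variance = (SD²/n) × [1 − ρw − ρwp + n·ρwp].
3. Variance under the service-only model: SD²/n. The SE is 21.4/√33 = 3.73 or 21.4/√38 = 3.47.
4. Variance ratio VR = 1 − ρw − ρwp + n·ρwp.
5. True type I error = 2·P(Z > 1.96/√VR).
6. Power of the ward-level t test for 13 points: noncentral t, 6 df, noncentrality 13/true SE.

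**Results at ρw = 0** (n = 33 / n = 38):

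| ρwp | VR | True SE | Type I error | Power of ward-level test, 13 points |
|---|---|---|---|---|
| 0 | 1.00 / 1.00 | 3.73 / 3.47 | .050 / .050 | .83 / .87 |
| .005 | 1.16 / 1.19 | 4.01 / 3.78 | .069 / .072 | .77 / .82 |
| .01 | 1.32 / 1.37 | 4.28 / 4.06 | .088 / .094 | .72 / .76 |
| .02 | 1.64 / 1.74 | 4.77 / 4.58 | .126 / .137 | .63 / .66 |
| .05 | 2.60 / 2.85 | 6.01 / 5.86 | .224 / .246 | .44 / .46 |

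**When there is no inflation.** VR exceeds 1 only if ρwp > ρw/(n − 1), that is, more than 1/32 to 1/37 of the stable ward ICC. At ρw = .05 and ρwp = 0, VR is .95 and the type I error is .044, slightly conservative.

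**Simulation check** (n = 36, 4,000 trials per setting, service entered as a fixed effect in place of its random intercept; Monte Carlo SE at .05 is √(.05 × .95/4000) = .003):

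| ρw, ρwp | Service effect only | Ward intercept only | t test on 8 ward changes |
|---|---|---|---|
| 0, 0 | .049 | .049 | .047 |
| .05, 0 | .045 | .050 | .045 |
| .02, .005 | .070 | .072 | .049 |
| .04, .01 | .090 | .094 | .051 |
| .03, .02 | .130 | .136 | .048 |
| 0, .05 | .243 | .246 | .054 |

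The simulation agrees with the formula. A ward intercept alone does not repair the test; the ward-level analysis does.

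**The case against.** The strongest reply is that service may be a loose word for ward. Under Implementation Measures the article counts 8 site/service cases, although two sites and two services make 4, and the sample size section groups patients by discharge unit. On that reading the named cluster is the right one, and the argument that it cancels falls away. This has some force as a matter of wording, but it conflicts with how Study Design and Population and Recruitment use the term. It also does not rescue the test: a ward intercept without a ward-by-period term gave .094 and .246 in the simulation at ρwp of .01 and .05.

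A second reply is that random-effect structure and degrees of freedom are commonly left to the analysis plan. That is fair for the degrees of freedom and the exact random effects: the article states neither a large-sample test nor an intercept-only model, and the calculation above assumes both. It does not excuse the cluster level, which the article does state.

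A third reply is that the ward-by-period ICC is unknown and could be near zero. That stands, and it makes the consequence conditional.

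**Conclusion.** The named cluster level is wrong for this design. A service contains both arms, and its effect cancels from the contrast that the protocol plans. Whether the CTM-3 test is thereby anti-conservative depends on ward-by-period variation. Over assumed ICCs of 0 to .05, the true type I error of a nominal 5% test runs from about 5% to 22-25%; at .01 it is about 9%. Both the size of the ICC and its stability over time are assumptions.

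A reader might infer more than the document supports in three ways:

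- **That the primary p-value is certainly too small.** With only stable ward differences it would be slightly too large.
- **That the larger inflation of a between-ward comparison in the intervention period alone applies.** The planned contrast is a difference in differences, which removes stable ward effects.
- **That AQoL-4D intervals are too narrow by the same amounts.** AQoL-4D is measured repeatedly in the same patients; the formula here is for one CTM-3 score per patient, with different patients in each period. The cluster level raises the same question there, but its size was not computed.

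**What to change.** In the Phase 2 analysis paragraph, replace service by ward. State random effects for ward and for ward-by-period, site-service as a fixed effect with 4 levels, and a small-sample correction (Kenward-Roger or Satterthwaite), which leaves about 6 degrees of freedom for the treatment contrast. Equivalently, compare the 8 ward-level post-minus-pre changes, 4 against 4, with a t test; a site-service main effect cancels from these changes, so 8 − 2 = 6 degrees of freedom remain. Use the same cluster level for the other outcomes, and use ward, service and site-service consistently throughout. Label the separate service analyses descriptive: with one ward per arm in each site-service, ward and treatment cannot be separated there. State the ICC assumed.

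The change needs no new data and does not touch patient care. The price is precision. The critical value rises from 1.96 to 2.447, so intervals are about 2.447/1.96 = 1.25 times as wide even without ward-by-period variation, and wider with it. Power for 13 points falls below the stated .80 if such variation is present: about .72-.76 at an ICC of .01 and .63-.66 at .02. The protocol should say so.
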